**Methods:**

The study corresponds to phase 2 of the Medical Research Council (MRC) complex interventions guidelines which cover the development and feasibility testing of an intervention. The work is in three stages. The development, adaptation and implementation of the Structured Preparation before Alcohol Detoxification (SPADe) intervention (stage 1), a randomised feasibility study with economic evaluation (stage 2) and a qualitative study (stage 3). Fifty participants will be recruited from two community alcohol treatment services in England. Participants will be randomised in two arms: the treatment as usual arm (TAU), which includes planned medically assisted detoxification and aftercare and the intervention arm in which participants will receive structured group preparation before detoxification in addition to TAU. The main outcomes are duration of continuous abstinence with no incidents of lapse or relapse, percentage of days abstinent and time to relapse.

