All instruments will be administered by research assistants in face-to-face assessments with participants. These assessments will take place at a convenient location for each participant, including their home. Research assistants (RA) will be fully trained to administer all outcome measures (see Table 1 below).

**Table 1 Tab1:** The use of instruments at different time points

Instruments	Baseline	3 months	6 months	12 months
TLFB (previous 90 days)	v	v	v	v
SADQ	v	v	v	v
AUQ	v	v	v	v
ICT	v	v	v	v
EQ-5D-5 L	v	v	v	v
Self-reported participation in aftercare		v	v	v

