#### Randomisation and masking

Once consented, participants will be randomised using a third-party web-based randomisation system which will ensure concealed allocation. Participants will be stratified according to the number of previous detoxifications (> 2 vs ≤ 2) and site. Randomisation will have a random block size [2–4]. Research assistants will be blind to the randomisation of the opposite study site and will conduct those follow-up interviews. Any breach in blinding/unmasking, a common problem with single-blind trials, will be monitored by asking the research assistants to report any such incident, to ensure that the research assistants are not aware, as far as possible, to which group the individual was allocated in the opposing study site.

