#### Statistical analysis

The main analysis will be based on the intention-to-treat principle considering all randomised clients according to the arm they were allocated. As the trial is a feasibility study, the main analysis is to be descriptive and estimate the potential effect sizes and parameters required for the sample size calculation, rather than formal hypothesis testing.

The feasibility outcomes will be summarised using descriptive statistics where appropriate. The potential primary and secondary outcomes will be summarised by arm, as well as completion rates estimated for each outcome measure. Duration of continuous abstinence, as measured from randomisation, and the time to relapse, as measured from the end of the intervention, will be analysed using a Kaplan-Meier curve and log-rank test. The percentage of days of abstinence (PDA) will be analysed using a regression model. Formal hypothesis tests and confidence intervals will be conducted although due to the nature of this trial, they will be treated cautiously and the main focus will be on the completion rate of outcomes and the estimation of parameters required for a sample size calculation for the main trial.

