## Discussion

The SPADe trial builds on previous work completed by the authors, which has shown that a structured preparation approach prior to alcohol detoxification can improve overall capacity of the treatment pathway by increasing patients’ engagement and by reducing dropout rates from detoxification [6, 15]. Two open studies indicated that the intervention improves outcomes (continuous abstinence) at 3 [15] and 6 months [16]. A qualitative study with service users who have completed the intervention [17] and a process study [33] have indicated that the theory-based intervention works as expected and predicted by the underpinning theory.

This feasibility trial will help us to answer questions of acceptability of the intervention by wider group of service users, carers and service providers. It will provide evidence on implementation issues such as the training, supervision and overall support required to implement the intervention. In more detail will enable us to do the following:Measure the number of eligible participants and those not, willingness of clinicians to recruit participants, recruitment rate, loss to follow-up, adherence to the intervention and standard deviation of the primary outcome measures. This will ultimately inform the sample size calculation for a multi-centre clinical trial.Determine the acceptability of randomisation to service users, through its effect on recruitment, dropout rates and via qualitative interviews.Determine, through response rates to questionnaires, the appropriateness and the acceptability of the outcome measures to service users, in order to explore the suitability of our chosen secondary outcome measures, that is, percentage of days of abstinent, service use and health-related quality of life.Estimate the time needed to collect and analyse baseline and outcome dataExplore the utility of the health-related quality of life instrument (EQ-5D-5 L) (see the ‘Outcome measures’ section) in allowing the estimation of quality-adjusted life years in the sample.

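### The stated log-rank test is not stratified by the randomisation factors, and the PDA regression is not tied to them or to baseline TLFB; precision is lost if these are prognostic

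*Protocol article*

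**What the plan says.** Protocol article, Randomisation and masking: "Participants will be stratified according to the number of previous detoxifications (> 2 vs ≤ 2) and site". That makes 2 × 2 = 4 strata, with small random blocks within them. The planned total is 50 (Abstract, Methods).

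Protocol article, Outcome measures, Table 1: TLFB, covering the previous 90 days, is taken at baseline and at 3, 6 and 12 months. A baseline PDA is therefore available from the same instrument that gives the follow-up PDA.

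Protocol article, Statistical analysis: duration of continuous abstinence and time to relapse "will be analysed using a Kaplan-Meier curve and log-rank test". For the third candidate primary outcome, "The percentage of days of abstinence (PDA) will be analysed using a regression model". No strata are named for the test, and no covariates are listed or excluded for the regression. The same section makes description and parameter estimation the main aim, and says that tests and confidence intervals will be read with caution.

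Protocol article, Discussion: the quantities meant to inform the main-trial sample size include the "standard deviation of the primary outcome measures". No residual SD and no baseline-to-follow-up correlation is mentioned.

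**The concern.** Stratified randomisation balances the arms on site and prior detoxifications, which takes the between-stratum variation out of the arm comparison. An analysis that ignores the strata leaves that variation in its error term. If the factors predict outcome, the reported standard error is larger than the true sampling variability of the estimate, so intervals are too wide and tests conservative.

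The article gives its own reasons to expect prior detoxifications to matter. The Background links repeated detoxification to stronger craving and to changes that may contribute to relapse. The Outcome measures section describes growing impairment, as detoxifications accumulate, on a task meant to model contributors to relapse. For site, the Economic evaluation section accepts that usual care may vary.

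Baseline PDA is a separate matter. It is not a stratifier, so chance imbalance is possible among 50 people, and adjusting for it can reduce genuine sampling variance.

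At stake are the precision of the effect estimates and, for PDA, whether the variance passed to the main trial matches the analysis that trial would use.

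**Working it through.** The article gives no SD, effect size, hazard ratio, power or derivation of N = 50, so there is no planned figure to reproduce. The check asks how large the effect could be under stated assumptions.

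**Inputs from the article:** N = 50; four strata (site × prior detoxifications); random blocks, taken as 2 or 4.

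**Assumed:** sites equally likely; 40% with more than two prior detoxifications; residual SD 1; arm effect 0.6 (linear model) or log hazard ratio −0.6 (time outcomes), set to 0 for type I error; exponential event times with administrative censoring; 3,000 simulated trials per setting.

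**1. Linear model (PDA type).** The arm-only model is compared with one adding site, prior detoxifications and a baseline covariate. With coefficient b per stratifier and c for baseline, R² = (0.49b² + c²) / (0.49b² + c² + 1), where 0.49 = 0.25 + 0.24 is the variance of the two binary factors.

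| b, c | R² | Mean SE, arm-only | Mean SE, adjusted | Ratio | Type I error, arm-only / adjusted | Power, arm-only / adjusted |
|---|---|---|---|---|---|---|
| 0, 0 | 0 | 0.282 | 0.285 | 1.01 | 0.045 / 0.049 | 0.54 / 0.53 |
| 0.3, 0.3 | 0.12 | 0.299 | 0.285 | 0.95 | 0.042 / 0.055 | 0.51 / 0.54 |
| 0.5, 0.5 | 0.27 | 0.330 | 0.285 | 0.86 | 0.041 / 0.055 | 0.43 / 0.54 |
| 0.8, 0.6 | 0.40 | 0.365 | 0.285 | 0.78 | 0.028 / 0.053 | 0.33 / 0.52 |

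Two effects are mixed here. At R² = 0.40 the arm-only estimate has a true sampling SD of 0.333 against a mean reported SE of 0.365, and 0.365 / 0.333 = 1.10. That 10% overstatement comes from ignoring the strata. The rest of the gain, from 0.333 to 0.288 (the sampling SD of the adjusted estimate), is genuine variance reduction, mainly from the baseline covariate.

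**2. Cost if nothing is prognostic.** For three covariates under simple randomisation, the approximate SE ratio is √(1 − R²) × √(47/44). At R² = 0 this is 1.034, and it breaks even at R² = 1 − 44/47 = 0.064. The simulated cost is smaller (1.01) because stratification already balances two of the three covariates.

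**3. Log-rank test**, unstratified against stratified by the four strata:

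| Log hazard ratio per factor | Type I error | Power |
|---|---|---|
| 0 | 0.051 / 0.049 | 0.41 / 0.39 |
| 0.3 | 0.048 / 0.051 | 0.44 / 0.43 |
| 0.5 | 0.044 / 0.049 | 0.43 / 0.46 |
| 0.8 | 0.034 / 0.056 | 0.37 / 0.45 |

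Stratifying pays only when the stratum effects are moderate or strong. The average stratum holds 50 / 4 = 12.5 people, which explains the small loss when they are weak.

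**4. Planning variance, PDA only.** Residual SD = marginal SD × √(1 − R²), so the sample size of an adjusted main trial scales with 1 − R². As an illustration (standardised difference 0.4, 80% power, two-sided 5%), n per arm = 2(1.96 + 0.842)² / 0.4² = 98.1, rounded up to 99. With R² = 0.10 it is 98.1 × 0.90 = 88.3, so 89. With R² = 0.25 it is 98.1 × 0.75 = 73.6, so 74.

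**The case against.** The strongest reply is that a condensed article has been silent, not wrong. Covariate lists, and whether a test is stratified, are commonly left to the full protocol or SAP, and neither is shown. For PDA this reply largely stands. A reader might infer that the regression ignores the strata and baseline, but the sentence neither lists nor excludes covariates, and a bare comparison of two arms would hardly need a regression model. For the time outcomes it stands less well: a specific test is named, and carried out as named it is the unstratified one.

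A second reply is that the loss is hypothetical. The article links repeated detoxification to relapse but gives no variance explained. It also plans to standardise usual care across sites. Entrants are moderately or severely dependent and seeking to stop, so baseline PDA may have a narrow range and predict little. This stands: the size is unknown and could be nil.

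A reader might also infer that the planning SD will be too large. The article does not support that. The marginal SD is the correct input for an unadjusted main trial and a usable start for an adjusted one, since the correlation can be estimated from the TLFB data being collected. The log-rank outcomes have no planning SD at all. Moreover, with 50 complete observations a normal-theory 95% interval for an SD runs from about 0.84 to 1.25 times the estimate, so a 5% shift from adjustment would be within sampling error.

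Finally, the tests and intervals are secondary and to be read cautiously. That limits the importance of the point but does not remove it, because effect sizes and planning parameters are what this trial is meant to supply.

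**Conclusion.** The point holds in a limited, conditional form. The log-rank test as stated does not follow the stratified randomisation, and the PDA regression is not tied to the stratifiers or to baseline TLFB. If these variables are prognostic, the comparison is conservative and less precise than the design allows; if they are not, adjusting gains nothing or costs a little.

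The size rests on assumed prognostic strength. For PDA, R² of 0.12 to 0.27 implies a standard error about 5% to 14% smaller with adjustment. For the log-rank test, the change in power from stratifying runs from about −0.02 with no stratum effect to +0.08 with a log hazard ratio of 0.8 per factor.

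The consequence is lost precision in cautiously read analyses. Nothing here shows bias, and unadjusted type I error was at or below about 0.05 in every setting. The documents do not show that the PDA analysis is unadjusted, that standard errors will certainly be too large, or that the raw SD is a wrong planning figure.

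**What to change.** Three changes of wording in the Statistical analysis section, or in the SAP if it does not already say so:

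- **Time outcomes:** stratify the log-rank test by site and prior detoxifications (> 2 vs ≤ 2), or report a hazard ratio from a Cox model stratified by or adjusted for both. With about 12 people per stratum, the adjusted Cox model is the less wasteful choice if any stratum turns out sparse.
- **PDA:** include arm, site, prior detoxifications and baseline PDA in the regression.
- **Planning parameters, PDA only:** report the adjusted residual SD and the baseline-to-follow-up correlation beside the raw SD, so that the main trial can be sized for either an adjusted or an unadjusted analysis.

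No new data are needed. The cost is a few degrees of freedom out of 50 and a possible small loss of power if the factors are not prognostic.

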#### Economic evaluation and analysis

The economic evaluation that will run alongside the future trial will assess the cost-effectiveness of the SPADe intervention, compared to usual care, from the NHS and wider public service perspective. Economic evaluation is required in the feasibility study to inform decisions about how costs and outcomes would be measured in any future definitive trial.

The feasibility study will seek to gain an understanding of the main resource items for which comprehensive data collection would be required in the main trial. The resources involved in delivering the intervention will be collected from providers and will cover human resources, facilities, materials and overheads, so that full economic costs and average costs per participant can be calculated. Usual care (received by both arms) may vary. Hence, data on care provided will be collected on an individual client basis from clinic records so that variability can be explored both within and between groups.

Alcohol dependence can give rise to significant use of health, social and criminal justice services. The cost of implementing SPADe may be offset if it results in increased numbers of successful detoxifications and consequent reductions in alcohol-related utilisation of these services. To capture this possible effect, data on service utilisation will be gathered retrospectively from participants at 3-, 6- and 12-month assessments by self-report. The Client Service Receipt Inventory, customised in collaboration with service users, will be used for this purpose. Included items will cover GP, mental health services, specialist alcohol services, A&E attendance, inpatient stays and contact with social and criminal justice services. Items of service use will be converted to costs (British pounds, 2017) using nationally validated sources [28, 29] and national reference costs for secondary care (https://www.gov.uk/government/publications/nhs-reference-costs-2012-to-2013). Service use data will be analysed descriptively to assess validity.

The feasibility study will also explore the properties of the alternative primary outcomes to assess their value as measures of effectiveness for the full economic evaluation. The health-related quality of life outcome for the economic evaluation will be EQ-5D-5 L, measured at each assessment point, from which a standardised unit of measurement—the quality-adjusted life year (QALY)—can be obtained. A preliminary cost-effectiveness analysis will be undertaken to determine the likely advantage of conducting a full economic evaluation. Total and per participant costs will be compared between groups to assess whether overall there are cost savings associated with the SPADe intervention, compared to usual care, and how these compare with client outcomes.

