### Stage 2—feasibility study

#### Design

This is a single-blind (outcome assessor blind to allocation), parallel, two-arm, feasibility RCT comparing the clinical effectiveness of SPADe as an adjunct to treatment as usual (TAU), against TAU. Participants will be assessed at baseline, 3, 6 and 12 months following randomisation. Additionally, qualitative interviews will be carried out at 3 and 9 months (see stage 3 below).

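### The service-use inventory covers specialist alcohol services within the blinded follow-up visits and is likely to disclose allocation for some SPADe attenders

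*Protocol article*

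**What the plan says.** The Design section of the protocol article describes a "single-blind (outcome assessor blind to allocation), parallel, two-arm, feasibility RCT". Randomisation and masking explains how this is achieved: "Research assistants will be blind to the randomisation of the opposite study site and will conduct those follow-up interviews". Any breach "will be monitored by asking the research assistants to report any such incident".

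The Outcome measures section says how follow-up is conducted: "All instruments will be administered by research assistants in face-to-face assessments with participants". Two of the candidate primary outcomes, duration of continuous abstinence and percentage of days abstinent, come from the Timeline Followback (TLFB). The third, time to relapse, is also defined by self-report.

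The Economic evaluation and analysis section adds a customised Client Service Receipt Inventory, for which "data on service utilisation will be gathered retrospectively from participants at 3-, 6- and 12-month assessments by self-report". Its content is listed: "Included items will cover GP, mental health services, specialist alcohol services, A&E attendance, inpatient stays and contact with social and criminal justice services". These items are then turned into costs. For usual care the same section names a second source: "data on care provided will be collected on an individual client basis from clinic records". Resources used to deliver SPADe come from providers, and SPADe attendance comes from the facilitators' record (Outcome measures).

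**The concern.** The blinding scheme keeps the assessor away from allocation at the other site, but the data collection then puts questions about the service that delivers SPADe into the assessor's own visit. A participant who answers accurately may mention the preparation groups. That would come from the planned questions and not from a chance slip, and it could happen at the first outcome visit.

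What is at stake is mainly the TLFB, where an assessor who knows the arm may probe or code differently. The study exists to estimate effect sizes and sample-size parameters, to choose a primary outcome for the definitive trial and to decide how costs should be measured there. Assessor bias in the drinking data would feed into the first two. An unblinding inventory could also be carried forward into the main trial.

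**Working it through.** The protocol gives no figure to reproduce here. The check sets the sections side by side, with one small count.

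**1. Does the inventory fall within the blinded visits?** Service use is collected at the 3-, 6- and 12-month assessments. Research assistants from the opposite site conduct follow-up and administer all instruments face to face. The inventory is not in Table 1 and no sentence names its administrator, so this step combines three sections. No separate administrator is mentioned.

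**2. Would the answers carry detail?** Item wording is not given. However, the answers are to be converted to costs, and per-participant costs are to be compared between groups. Costing needs the amount and type of contact, which a bare yes/no does not supply.

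**3. Does that detail differ by arm?** Planned contacts before detoxification, from Trial arms:

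| Arm | One-to-one key-worker meetings | SPADe groups | Total |
|---|---|---|---|
| Usual care | 3–4 | 0 | 3–4 |
| SPADe plus usual care | 3–4 | 6 | 3 + 6 = 9 to 4 + 6 = 10 |

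The type differs as well. In usual care, groups are described only under aftercare, so a group attended before detoxification points to SPADe.

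**4. Does the 3-month visit cover the SPADe period?** Six weekly sessions span 5 × 7 = 35 days from first to last. The inventory's recall period and the SPADe start date are not stated. If recall reaches back to randomisation and sessions start within a few weeks of it, the course lies inside the roughly 90 days before the visit.

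**5. How many participants and visits?**
- Participants: the allocation ratio is not stated. Assuming 1:1, the ceiling is 50 / 2 = 25 SPADe participants. The real number is lower, because some will not attend the groups or the visit, and non-English speakers receive SPADe one to one, which is harder to tell from key-working.
- Visits: disclosure at 3 months would affect the other two of the three follow-up visits only if the same assistant returns. Cross-site allocation makes that plausible, but it is not stated.

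**6. Does instrument order protect the outcomes?** No order is given. Placing the inventory last would protect the 3-month TLFB. It would not protect the 6- and 12-month TLFB if the same assistant came back.

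**7. Is there a preventive safeguard at the visit?** The site swap keeps the assistant from learning allocation locally. Beyond that, the text asks assistants to report incidents, which records unblinding after the event.

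**The case against.** The strongest reply is that disclosure is inferred. The protocol says only that the inventory covers specialist alcohol services. Both arms use the same service and both may attend aftercare groups, so a yes/no item would be answered alike and a total count would be blurred. This stands as a limit on the claim. A reader might infer that SPADe attendance is revealed for everyone from 3 months, and usual care by the absence of groups; the documents do not support either reading. What remains is that costing makes counts and types of contact the likely form of the item.

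Second, the inventory may be self-completed. That is not excluded. But the SADQ and AUQ are called self-completion questionnaires and still fall among the instruments that research assistants administer, so self-completion alone does not keep answers from the assistant.

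Third, the impact is limited. Participants know their arm, so self-reported drinking is open to reporting bias whatever the assessor knows. The SADQ and AUQ are self-completed and the incentive conflict task is a performance test. The main analysis is descriptive, tests are treated cautiously, and the protocol acknowledges that unmasking is common. All of this is fair. It narrows the issue to the assessor's part in the TLFB.

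Fourth, instrument order and disclosure prompts are details that an article may leave to the full protocol. Their absence is not the finding. The finding is the stated placement of this item within the blinded visits.

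Two further inferences should not be drawn. One is that the inventory is the only follow-up source for A&E and inpatient events: it is the only named service-use source for A&E, but clinic records may hold inpatient detoxification and a safety-reporting route is named. The other is that alcohol-service costs will be counted twice: no costing rule that adds the two sources is shown.

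**Conclusion.** The point holds as a likely, partial and avoidable route of unblinding. The protocol places an inventory covering specialist alcohol services inside visits run by assessors meant to be blind, and it states nothing that stops the answers from disclosing allocation.

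The gap in planned pre-detoxification contacts, 9–10 against 3–4, is large enough to be informative if number and type are recorded. About 25 participants and two later visits are ceilings, resting on 1:1 allocation, full attendance and disclosure, and the same assistant returning. The size of any resulting bias in the TLFB outcomes cannot be estimated from the document. The change is worth making because it is cheap and removes a cause of assessor bias instead of only recording it.

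**What to change.** - Take contacts with the recruiting alcohol service (SPADe, key-working, detoxification) from facilitator, provider and clinic records, all of which the protocol already plans to use.
- Limit the assessor-administered alcohol-service item to other providers, or have that item self-completed and returned sealed.
- Keep the A&E, inpatient, GP, mental health, social and criminal justice items. Keep the aftercare log whole, since it is a stated secondary outcome. Place all of these after the TLFB, SADQ, AUQ and incentive conflict task.
- Ask participants at the start of each visit not to mention preparation groups.

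The work is an edit to an inventory that is being customised anyway, plus a fixed instrument order. The cost is that recruiting-service use would rest on records, so self-report could not be checked against them for that item. This matters somewhat, because the protocol intends to assess the validity of the service-use data; the sealed option would keep the check. Recruitment had finished by the time the article was accepted, so the change applies to follow-up visits still outstanding and to the design of the definitive trial.
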